### 2.7. Recruitment of Study Participants

The study will be conducted in the 18 selected secondary schools as clusters; each school will be randomly assigned to the intervention study group or the control study group. Each school cluster will be independent, with no crossover of staff/students and defined as a natural cluster for the purpose of the trial. Each arm of the study will have nine schools (clusters).

The selection of the 18 study schools (clusters) will be conducted as per the criteria described in Section 2.6 (sampling) and each of the 18 schools will be randomly assigned to either the intervention (with SBSRH package) or the control group (without SBSRH package). This means that both the intervention arm and control arm had will have a total of nine schools each.

Within each school, the 1080 study participants will be selected systematically based on the inclusion criteria described in Section 2.2 (selection criteria). The recruitment of the study participants will be done independently by the researchers and research assistants. This will be done at school using the systematic sampling framework described in Section 2.6. The process is anticipated to take place within one month for all the 18 schools. Only girls who meet the inclusion criteria will be enrolled into the study. The participants will be informed about the study objectives without revealing the study hypotheses. Upon recruitment, each participant with their parent will be required to ascent and consent, respectively, by signing formal ascent and consent forms. Data collection (base line) will be done, an SBSRH package will be provided in the nine intervention clusters (schools) and follow-up is done for 12 months. An end of study assessment will be conducted after twelve months and data will be analyzed.

### 2.8. Description of the Intervention

The intervention for the experimental group will be a three tier adolescent tailored SRH service package provided at school. The School-Based Sexual and Reproductive Health (SBSRH) package will be provided for 12 months and will include provision of ASRH information and awareness sessions using stepping stones methodology, in-school ASRH services and referral to public health facilities. Follow-up will be done at 6 months and 12 months from the start of the study.

#### 2.8.1. Tier 1: In-School ASRH Education Session

The health education sessions will provide information and create awareness on HIV, pregnancy, safer sex, Gender Based Violence, HIV, pregnancy, sexually transmitted infections (STIs), gender norms, effective communication and safe sex practices, sexuality and self-assertion. The Stepping Stones curriculum and the National sexuality framework in Uganda will be used as the standardized behavioral change package using the interpersonal peer to peer approach. 10 sessions (communication, how we act, sex, love, gender based violence, contraceptives, HIV prevention, safer sex practices, assertiveness, supporting one another and self-reflection) will be conducted for the participants by fellow trained peers and knowledge change as well as behavioral change assessed. Implementation of sessions will be done in small groups of 15–20 girls (peers). Peer facilitators will be trained and supported to conduct the small group discussions on SRH and HIV prevention. The researcher, research assistants, SRH nurse and senior woman teacher in-charge of SRH will supervise these sessions.

#### 2.8.2. Tier Two: In-School Adolescent Sexual and Reproductive Health (ASRH) Services

ASRH services will be provided at the intervention school (on-site) in an allocated room/school clinic. They will be available and accessible to all students regardless of whether they are participating in the study or not. Key services will include information, sensitive counseling, STI screening and treatment, HIV testing, contraceptives (where permitted), referral and general medical care. These will be conducted once a week by a skilled health worker recommended by the health unit in-charge at the school premises from 7:00 am to 6:00 pm. The SBHCs will be operational only during the school terms; however, their operation during the holiday will be dependent on the need and authorization from the school administration.

#### 2.8.3. Tier Three: Referrals to off-Site Public Health Facilities

The students identified in need of advanced ASRH care such as post abortion care, antenatal care and HIV treatment will be referred to primary or tertiary public health facilities for further management. Details of the reasons for referral will be recorded and a Ministry of Health (MOH) referral form filled and given to the student. The health workers at the public health facilities nearest to the school will be sensitized about the study and possible referrals to be made and a mechanism of management of the referred cases will be developed to prevent delays and stigma associated with adolescent SRH care. The district ASRH officer will take lead in this activity for ownership but also to monitor the response of health workers during the implementation.

**Follow-up:** Follow-up of the participants will be done for 12 months and data will be collected at the start of the study, after six completed months and at the end of the study after 12 months. Data on student demographics, services received and perception towards the service and provider will collected on each clinic day to assess the level of utilization and the most sought after services.

**Control Group**: The clusters in this arm will not receive any intervention from the research team. However, the participants are free to continue accessing services from the nearby facilities as has been the case prior to the study.

**Data Collection Methods:** Quantitative data will be collected using the survey method three times that is at the start of the study (0 months), six months and at the end of the study after 12 months. Qualitative data will be collected once during the 12 months of the study through interviews and discussions with the identified stakeholders. This is intended to provide subjective and relevant information to enrich the quantitative data on adolescent pregnancy in the Hoima District.

**Data Collection Tools:** Quantitative data will be collected using a self-administered questionnaire while Qualitative data will be collected using the Key Informant Interview guide and discussions using the Focus Group Discussion guides. Additional qualitative data will be collected at other SRH service delivery point to provide a snapshot on the level of utilization of services provided; this will be done using an SRH utilization register.

**Participants:** The respondents to the questionnaire, key informant interview and focus group discussions will be categorized as shown in Table 1.

**Validation Procedure:** The questionnaire to be used in this study will undergo three types of validity, which include; (1) content validity; (2) criterion- related validity; and (3) construct validity. This validation procedure will ensure that the questionnaire accurately measures what it aims to do, regardless of the responder. A valid questionnaire will help to collect better quality data with high comparability, which reduces the effort and increases the credibility of data.

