### 2.6. Sampling Techniques

The study will use multi-stage sampling technique to select the study population. The Hoima District was purposively selected because of the high (29%) adolescent pregnancy and the thriving economic activities, which further increase the vulnerability of the adolescent girls to pregnant. The District has 36 registered secondary schools in four constituencies Kigorobya, Bugahya, the Hoima municipality and the Buhaguzi counties.

**Cluster Sampling:** Clusters of adolescent girls attending secondary school who represent the target population will be identified and included in the sample [34]. This will be used to increase the level of efficiency of sampling and each cluster will be considered as a sampling unit. In this study, the clusters will be secondary schools registered and operational in the Hoima District; a list of all clusters (schools) will be generated from the District Education Office and clusters will be ranked according to the level of school dropout rate. The top 18 clusters (schools) with the highest dropout rate will be considered for the study. The selection will be based on the judgment of the researcher using drop-out rates at each school within the population in the Hoima District. The schools to be selected from each county should rank highest in dropout rates of adolescent girls in the last 12 months prior to the study. Four to five secondary schools with the highest student enrolment and highest school dropout rates will be selected from each county. The statistics will be derived using the annual school dropout reports from the Hoima District Education Officer (DEO) and the Chief Administrative Officer (CAO). In addition to the school dropout rates, the schools to participate in the study will meet the following requirements:Permission to conduct outreach SRH services at school and willingness of the head teacherAvailability of SRH focal person usually called the ‘senior woman teacher’Proximity to a functional public health center (within 5–10 km)Access to eligible studentsGeographical location of the school

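### Tier 3 works on the public facilities nearest intervention schools, and no stated rule keeps control schools from sharing them, so an unchanged comparator is not secured

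*Protocol article*

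**What the plan says.** **Intervention.** Tier 3 (protocol article, Section 2.8.3) reaches outside the school: "The health workers at the public health facilities nearest to the school will be sensitized about the study and possible referrals to be made". It continues: "a mechanism of management of the referred cases will be developed to prevent delays and stigma associated with adolescent SRH care". A district-level officer leads and monitors: "The district ASRH officer will take lead in this activity for ownership but also to monitor the response of health workers during the implementation".

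**Comparator.** The control paragraph in the same section reads "The clusters in this arm will not receive any intervention from the research team", and adds that "the participants are free to continue accessing services from the nearby facilities as has been the case prior to the study".

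**Independence.** Section 2.7 states: "Each school cluster will be independent, with no crossover of staff/students".

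**Selection and allocation.** Section 2.6 takes 18 of the district's 36 registered secondary schools, four to five per county, ranked mainly on dropout. Each must lie within 5 to 10 km of a functional public health centre. The names of the 18 schools are drawn from a basket, nine per arm. The Abstract says instead that allocation is stratified by location.

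**Outcomes.** Section 2.1.2 lists incidence of pregnancy, sexual and behaviour change, and utilization of SRH services as primary outcomes.

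**The concern.** Both arms use the same kind of public facility, and the trial works on some of those facilities. If an intervention school and a control school have the same nearest facility, control girls who go there meet staff whom the trial has sensitised. For those schools the comparator is no longer access as it was before the study. The statement about staff and students does not cover this route, because neither has to cross between schools for it to operate.

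Utilization of SRH services is the outcome most directly exposed: control girls could use more services, or use them more readily, because of the trial. Any effect on pregnancy would be diluted in the same direction. Analysis by intention to treat (Sections 2 and 3) keeps girls in their allocated arm but does not undo such dilution. If facility use is not recorded by school, a small or null difference would be hard to interpret.

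**Working it through.** **1. Does the stated design prevent sharing?**

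- *Basket draw, 9:9.* If two of the 18 schools share a facility, they fall in opposite arms with probability 9/17 = 53%.
- *Stratification by location.* If the strata are counties (an assumption; the article does not say), the probability is 2/3 = 67% in a stratum of four split 2:2. In a stratum of five split 2:3 it is (2 × 3)/10 = 60%. Stratifying puts both arms into each area, so it makes opposite-arm sharing somewhat more likely.
- *Eligibility.* Section 2.6 names geographical location among the school requirements but attaches no separation rule to it.

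These probabilities are conditional on a pair sharing. The article gives no facility list, map or count, so the number of such pairs is unknown.

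**2. What could spill over?**

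| Component | Where delivered | Reach to control girls |
|---|---|---|
| Tier 1, peer sessions (2.8.1) | Intervention school | None through a facility |
| Tier 2, weekly clinic, contraceptives where permitted (2.8.2) | Intervention school | None through a facility |
| Tier 3, staff sensitisation (2.8.3) | Nearest public facilities | Possible where the facility is shared |
| Tier 3, arrangement against delay and stigma (2.8.3) | Same facilities, for referred cases | Limited: a control girl who walks in is not a referred case |

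The needs Tier 3 names as examples are post-abortion care, antenatal care and HIV treatment. Two of these follow a pregnancy and none is primary contraception. Spillover is therefore likelier on utilization than on pregnancy.

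**3. The plan's sample size.** The risk of 0.29 is taken as that without the intervention, since Section 2.4.2 describes it as the current prevalence.

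- n = (1.96 + 0.842)² × [0.29 × 0.71 + 0.19 × 0.81] / 0.10² = 7.851 × 0.3598 / 0.01 = 282.5, stated as 283.
- Design effect 1 + 59 × 0.01 = 1.59; 282.5 × 1.59 = 449 per group, 898 in total.
- 898 × 1.10 = 988; 988/60 = 16.5, raised to 17 and then 18 clusters; 18 × 60 = 1080.

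The plan's figures reproduce. They assume the full 29% v 19% contrast.

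**4. Illustration of dilution.** Let c be the share of the 10-point pregnancy effect that reaches the whole control arm. The documents give no value for c.

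- After 10% loss: 540 × 0.9 = 486 per arm, 60 × 0.9 = 54 per school.
- Design effect 1 + 53 × 0.01 = 1.53; effective n = 486/1.53 = 317.6 per arm.
- Control risk p = 0.29 − 0.10c; power = Φ(|p − 0.19| / √{[p(1 − p) + 0.1539]/317.6} − 1.96).

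| c | Control risk | Difference | Power |
|---|---|---|---|
| 0 | 0.29 | 10 points | 84% |
| 0.1 | 0.28 | 9 points | 77% |
| 0.2 | 0.27 | 8 points | 67% |
| 0.3 | 0.26 | 7 points | 56% |

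The table shows what an assumed c would cost. It is not evidence of how large c is. The utilization outcome cannot be worked the same way, because the article gives no planning values for it.

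**The case against.** A reader might infer more than the text supports.

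- *That control girls are sent to the sensitised facilities.* They are only free to go on using what they used before.
- *That the comparator is altered and the schools are not independent.* This would need proof of shared facilities, and the article gives none. Section 2.7 ties independence to staff and students; it is incomplete on facilities rather than contradicted.
- *That control girls would receive improved care generally.* Sensitisation is about the study and possible referrals, and the arrangement against delay and stigma is for referred cases.
- *That 10 to 30% of the pregnancy effect would leak.* The preventive content sits mostly in Tiers 1 and 2, delivered in intervention schools. Even 10% across all nine control schools would need several to share a facility and many girls to benefit.

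It can also be said that an article may leave catchment lists to the full protocol, that an SRH utilization register is planned at other service points, and that dilution towards no effect would leave a positive result credible.

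These objections limit the size of the problem, and all four stronger readings should be set aside. They do not remove its core. The article states its draw and its comparator, and as stated neither protects the contrast. The register is described as a snapshot and is not tied to arm or school.

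**Conclusion.** The point holds in a limited form and is worth a cheap improvement. A facility-level part of the intervention acts on the kind of service control girls use, within one district, and no stated rule keeps schools in opposite arms from sharing a facility. Unchanged access in the control arm is therefore not secured, though it is not shown to be lost.

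The main exposure is the primary outcome of SRH service utilization. Dilution of the pregnancy effect is probably smaller and cannot be sized from the documents. The power figures (84, 77, 67 and 56% for c of 0, 10, 20 and 30%) rest on the plan's own risks and ICC, 10% loss, and an assumed spillover. The direction, if sharing occurs, is chiefly towards no difference.

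**What to change.** 1. **Before the draw**, list the nearest public facility of each selected school. Where two eligible schools share one, prefer the next-ranked eligible school with a separate facility, if there is one.
2. **In the existing 6- and 12-month questionnaires**, in both arms, add an item on which facility was used.
3. **Pre-specify a sensitivity analysis**, for utilization and for pregnancy, that sets aside control schools whose nearest facility was sensitised. It removes schools from one arm only, so it supports the main analysis and does not replace it. If no such school remains after step 1, report that instead.
4. **Reword the control paragraph in Section 2.8.3** so that it does not claim unchanged access where a facility is shared, and say whether facilities serving control schools will be sensitised.

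Forcing schools that share a facility into the same arm is not recommended as the default: it merges clusters and leaves fewer than nine independent units per arm.

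Cost: a list, one questionnaire item, a little more analysis, less precision in the sensitivity analysis, and possibly one or two substituted schools.

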## 3. Analysis

Analysis will be done using aggregate cluster-level analysis; regression analysis using individual patient data with robust standard errors; random-effects (Res) models using individual patient data; and population averaged models using individual patient data with regression coefficients estimated using generalized estimating equations (GEEs). In this study, data exploration will be done to visualize the general feature of the data then the key analysis will be by SPSS version 20 at both cluster and individual levels. Both descriptive and inferential statistics will be analyzed allowing for the association between SBSRH service and prevention of adolescent pregnancy (occurrence of pregnancy, sexual behavioral change). The intent to treat analysis will be used to analyze patients according to their random treatment assignment, which is the intended treatment, not the treatment actually received.

Descriptive summary statistics of the clusters and individuals such as frequencies, mean, medians and standard deviations will be used to describe the characteristics of the study population on sex, age, socio-economic, education level, pregnancy status and sexual behavior, among others. Summary statistics for categorical data will be displayed in form of mean, proportion, frequencies and percentages depending on the nature of the data.

To determine the association between the dependent and independent variables, a general logistic regression model will be employed and two steps will be followed. First, each variable will be entered into a binary logistic regression model. Second, variables that are found to be significant at a p-value of 0.05 will be fitted into a multiple logistic regression model to identify independent factors of influencing occurrence of adolescent pregnancy. Variables that remain significant at a p-value of 0.05 will be further analyzed using multivariate logistic regression model and variables will be identified as independent factors influencing incidence of pregnancy and behavioral change.

Based on the above logistical regressions, inferential statistics such as t-test and chi square test will be used to determine the similarity in the two groups using their baseline data (baseline comparison) and to determine relationships as well as associations between variables. Chi square tests will be used to test the relationships between categorical variables, while independent t-tests will be carried out to determine differences between the study groups for continuous variables with normal distribution.

Cluster level: The summary measure for each cluster (mean or proportion) will be calculated, because each cluster provides only one data point and the data will be considered to be independent while allowing standard statistical tests to be used. Multiple regressions will be used for the data summarized at the cluster level.

Individual level: During the two stage data analysis process, individual level covariates will be incorporated into the cluster analysis while accounting for the intra-cluster correlation, thus increasing the statistical power of the analysis. Statistical tests will be conducted taking into account for the clustering effect.

Qualitative data collected during the key informant interviews and focus group discussions will be transcribed and typed into a Microsoft Word computer program. These notes will be transcribed verbatim to ensure complete capturing of the responses of the study participants. Thematic analysis will be used to analyze qualitative data from key informant interviews and focus group discussions using the Atlas qualitative data analysis software version 7 (atlasti.com). Themes and sub-themes relevant to the objectives of the study will then be identified to enable development of qualitative coding and code definitions. Codes will be grouped into categories and then themes. The coded transcripts will be analyzed by running query reports and primary documents tables of codes by objective or theme and results will be used to explore the magnitude of the issues from the various focus group discussions and key informant interviews. Quotes illustrating meaning or key messages from the analysis will be selected based on the code count or how illustrative to the theme the quotes will be.

Structural equation modeling (SEM) using Analysis of a Moment Structures (AMOS) and Statistical Package for Social Sciences (SPSS) will be used to determine the statistical significance of the SBSRH model in the prevention of adolescent pregnancy. The constructs of the SBSRH model will be specified based on the theories that informed the research and the findings. Data of the identified constructs will be entered into the SEM software package. The package will fit the data to the SBSRH model and produces the results, which will include the overall model fit statistics and parameter estimates. Matrices of correlations and means will be used and relationships will be expressed as restrictions on the total set of possible relationships. The results feature overall indexes of model fit as well as parameter estimates, standard errors, and test statistics for each free parameter in the model.

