#### 2.4.2. Considerations

*π*T = Proportion of pregnant girls in group 1 approximately 29% (0.29). This is the current pregnancy prevalence in Bunyoro region (29%).

*π*C = Proportion of pregnant girls in group 2 approximately 19% (0.19). This is the expected reduction in prevalence of adolescent pregnancy after the intervention.
$$\begin{array}{lll} \mathrm{Effect}\mathrm{size} & = & 10\%[\delta \mathrm{Binary}=(\pi T-\pi C)],\mathrm{which}\mathrm{is}0.1\\ \alpha & = & 0.05(\mathrm{two}-\mathrm{sided})\\ \beta & = & 0.2\\ Z\alpha /{}_{2} & = & \mathrm{Desired}\mathrm{significance}\mathrm{level}\mathrm{at}5\%(1.96)\\ Z_{1-\beta } & = & \mathrm{Desired}\mathrm{power}\mathrm{at}80\%(0.842)\\ \mathrm{Type}\mathrm{of}\mathrm{test} & = & \mathrm{Two}-\mathrm{sided} \end{array}$$

Absolute risk reduction = 10%;

**Step One:** Formula for determining the number of subjects per group *^n^*_Individual_Binary_ for a two-sided significance level *α* and power 1 − *β*:$$\begin{array}{c} =\frac{{\left(1.96+0.842\right)}^{2}[0.29(1-0.29)+0.19(1-0.19)]}{{\left(0.29-0.19\right)}^{2}}\\ =(2.802)2[0.2059+0.1539]\\ =(7.851\times 0.3598)/0.01\\ =282.5\\ \sim 283\mathrm{individuals} \end{array}$$

**Step Two:** In order to adjust for the clustering effect, the sample size (*^n^*_Individual_Binary_) was inflated by a Design Effect (DE) to get an adjusted sample size (*^n^*_Cluster_Binary)_ [31]. Therefore, to determine the adjusted sample size per study group (*^n^*Cluster_Binary) for a Cluster Randomized Controlled Trial (cRCT), with a binary outcome, we multiply it with the Design Effect (DE):*^n^*_Cluster_Binary_ = *^n^*_Individual_Binary_ × Design effect
*^n^*_Cluster_Binary_ = *^n^*_Individual_Binary_ × [1 + (*m* − 1) *ρ*]
where *m* is the fixed cluster size and *ρ* is the Intra-cluster correlation coefficient (ICC). ICC is the ratio of the between-cluster variance to the total variance of an outcome variance and quantifies the correlation between the outcomes of any two individuals within the same cluster [31]. Since there is no previously published data/study in Uganda documenting the ICC, an ICC of 0.01 was considered because it is within the recommended inter-quantile range ICC (0.011–0.094) for previously undocumented ICC. Campbell and Walters [24] recommended a minimum cluster size of 50 subjects per cluster to cater for secondary outcomes; therefore, a fixed cluster size of 60 individuals was considered for this study.

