### 2.5. Number of Clusters

The minimum number of units to be able to achieve a 5% level of significance is four per arm assuming normality for the cluster level responses and the use of non-parametric test, Mann–Whitney *U*-test [24]. Campbell [31] further states that with three units per arm, it is within the bounds of chance that the outcomes in the three treatment arms are all greater than the outcomes in the three control arms; however, with four per arm, this is unlikely to happen by chance more than 1 in 20 times. Therefore, the minimum number of clusters is four per arm (eight in total) for an unmatched design or six matched pairs for a matched design.

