**To determine number of clusters needed (*n*_cluster):**
*n*_cluster = Total number of participants in the two groups (/fixed cluster size) = (*^n^*_Cluster_Binary × 2)/*m*_ = 988/60 = 16.5 ~17 clusters. 

In order to have the same number of clusters per arm, the number of clusters was increased to the nearest upper even number, which is 18 in this study. Therefore, the study will have a total of 18 clusters; nine clusters will be randomized to the intervention and nine clusters will be randomized to control group. This means that the sample size contains 1080 adolescent girls in 18 clusters.

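### Two of the four named analyses, robust-standard-error regression and GEE, run at about 7-9% type I error on 18 schools unless a small-sample correction is used, and nothing says the school-level analysis decides

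*Protocol article*

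**What the plan says.** Section 3 (Analysis) lists four approaches: an aggregate cluster-level analysis, "regression analysis using individual patient data with robust standard errors", random-effects models, and "population averaged models using individual patient data with regression coefficients estimated using generalized estimating equations (GEEs"). It places the key analysis at both school and individual level. Later in section 3, the cluster-level route is described as one summary per school analysed with standard tests. The individual-level route is described as allowing for the intra-cluster correlation and gaining power. No family is designated as the one that decides the pregnancy comparison. No small-sample correction is mentioned, and none is ruled out.

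On the number of schools, section 2.5 says that "nine clusters will be randomized to the intervention and nine clusters will be randomized to control group". Section 2.4.2 sets a two-sided alpha of 0.05 and 80% power for 29% against 19% pregnant. Section 2.5 also remarks, with reference to a Mann-Whitney test, that "The minimum number of units to be able to achieve a 5% level of significance is four per arm".

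**The concern.** Robust standard errors and GEE are the article's individual-level means of allowing for clustering, so a reader may assume that choosing them secures the 5% level. With few clusters they do not. The sandwich variance is built from school-level residuals. With nine schools per arm and no covariates it is too small by a factor of about 8/9. The statistic then behaves like a t on about 16 degrees of freedom, while standard practice refers it to a normal or chi-square distribution. Both errors act in the same direction.

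An ineffective package would be declared effective more often than the design allows, and confidence intervals would overstate precision. A report that rested its pregnancy result on the robust or GEE test would still be within the plan as written.

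**Working it through.** **Inputs from the article.** Two-sided alpha 0.05 (z = 1.96), power 80% (z = 0.842), rates 0.29 and 0.19, ICC 0.01, 60 girls per school (all section 2.4.2); 10% added for non-response (section 2.4); 9 + 9 schools (section 2.5).

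**The plan's own figure.** 2.802² × (0.29×0.71 + 0.19×0.81) / 0.10² = 7.851 × 0.3598 / 0.01 = 282.5. Times the design effect 1 + 59×0.01 = 1.59 gives 449 per group, 898 in total, and 988 after adding 10%. Then 988/60 = 16.5, rounded to 17 and raised to 18 schools. The stated figures reproduce.

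**Analytic type I error, no covariates, equal school sizes.** The uncorrected robust z equals t16 × √(9/8). The rejection rate at 1.96 is therefore 2·P(t16 > 1.96 × √(8/9)) = 2·P(t16 > 1.848) = 0.083.

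**Simulation under the null** (beta-binomial outcomes, 9 v 9 schools of 60, ICC 0.01, no stratification unless stated):

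| Test | Rejection rate |
|---|---|
| Uncorrected sandwich, z, p = 0.29 (100,000 trials) | 8.2% |
| Same, p = 0.19 | 8.4% |
| Fitted GEE, exchangeable, p = 0.29 (1,500 trials) | 7.1% |
| Fitted GEE, independence, p = 0.29 (4,000 trials) | 8.7% |
| Same, plus five individual-level covariates | 8.6% |
| Variance × 18/16, t on 16 df, p = 0.29 | 4.9% |
| t-test on school proportions, p = 0.29 | 5.0% |

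School sizes varying from 30 to 60 changed the uncorrected rate by less than 0.5 points.

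**Interval width.** Corrected over uncorrected: 2.120 × √(9/8) / 1.96 = 1.147, so about 15% wider.

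**School-level terms.** With three location terms, the approximation 2·P(t13 > 1.96 × √(13/18)) gives 12.0%. Simulations with three school-level terms gave 11.3% to about 14%, depending on ICC, estimator and draw.

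**Stratified draw analysed without county terms** (54 girls per school, p = 0.29, ICC 0.01). The uncorrected test rejected 8.3% with no difference between counties, and 7.1%, 5.8% and 4.5% with between-county standard deviations of 3, 4.5 and 6 percentage points. Those standard deviations are assumptions; the article gives none.

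**Power with the t reference (16 df), school-level standard error.**
- 60 girls per school: variance 0.3598 × 1.59 / 540 = 0.001059, SE 0.0325, non-centrality 0.10/0.0325 = 3.07, power 82.2%.
- 54 per school (10% loss): design effect 1.53, variance 0.3598 × 1.53 / 486 = 0.001133, SE 0.0337, non-centrality 2.97, power 79.7%.

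**The case against.** The strongest reply is that the article does not commit to the faulty version of these tests. It never says that the variance is uncorrected or that the reference is normal. Degrees of freedom and small-sample corrections are normally left to an analysis plan, which is not shown here. This stands as a limit: the rates above are conditional on the usual form. It does not dispose of the point, because the article fixes both the methods and the number of schools at which their usual form fails, and it gives the valid school-level test no precedence.

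Three stronger readings are tempting and are not supported.

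- *That every cluster-adjusted analysis in the plan misses 5%.* The aggregate school-level analysis is named first, is described again later in section 3, and holds about 5%.
- *That section 2.5 wrongly justifies the 5% level for the regressions.* That section gives only a minimum number of clusters for a rank test, and correctly: the smallest two-sided exact p is 2/20 = 0.10 with three per arm and 2/70 = 0.029 with four. Alpha is set in section 2.4.2, and the 18 schools come from 988/60.
- *That the error rate is 12% or more.* At the plan's rates this needs about three school-level terms. The abstract says allocation is stratified by location, but section 3 does not say that location enters the models. Outside the plan's rates, an outcome of 5% with an ICC of 0.094 gave 12.2%.

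It is also fair to say that a stratified draw analysed without county terms can push the rate down, to 5% or below if counties differ enough.

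**Conclusion.** The point holds in conditional form. If the pregnancy comparison is judged by an uncorrected robust-standard-error or GEE test on 18 schools, type I error is about 7-9% (8.3% analytically) instead of 5%, and 95% intervals are too narrow. Three location terms would raise this to about 11-14%, but the article does not state that they will be fitted.

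The figures assume beta-binomial outcomes, the article's rates and ICC, near-equal school sizes and, for the base case, no county differences. Random-effects models, the remaining family, were not assessed. A reader might infer that the trial has no valid test of its main comparison. The article does not support that: the school-level analysis is valid, but nothing says it decides.

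**What to change.** In section 3, add one of two statements:

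1. Any robust-standard-error or GEE test of the arm effect uses a small-sample-corrected variance and a t reference, with degrees of freedom equal to the number of schools minus the number of school-level parameters: 18 − 2 = 16 without school-level covariates, 18 − 5 = 13 with three location terms.
2. The arm effect is tested on the 18 school summaries by a t-test or a permutation test.

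If pregnancy turns out much rarer than planned and the ICC is high, the second is safer: at 5% and ICC 0.094 the corrected robust test still rejected 8.0%, the school-level t-test 3.8%.

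The cost is a sentence or two and a routine software option or short script. Intervals become somewhat wider, and power at the plan's own inputs is 79.7% to 82.2%. The number of schools can stay as it is, and section 2.5 needs no change.
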